## Abstract

**Background:** The incidence of Type 2 diabetes mellitus (T2DM) combined with non-alcoholic fatty liver disease (NAFLD) has risen over the years. This comorbid condition significantly increases the probability of cirrhosis, liver cancer, and mortality compared to the disease alone. The multi-targeted, holistic treatment efficacy of traditional Chinese medicine (TCM) plays a vital role in the treatment of T2DM and NAFLD. Jiedu Tongluo Tiaogan Formula (JTTF), based on TCM theory, is widely used in clinical treatment, and its effectiveness in lowering glucose, regulating lipids, improving insulin resistance, and its pathways of action have been demonstrated in previous studies. However, the mechanism of this formula has not been investigated from a metabolomics perspective. Moreover, high-quality clinical studies on T2DM combined with NAFLD are lacking. Therefore, we aim to conduct a clinical trial to investigate the clinical efficacy, safety, and possible pathways of JTTF in the treatment of T2DM combined with NAFLD using metabolomics techniques.

**Methods:** A total of 98 participants will be recruited to this clinical trial and randomly assigned to either a treatment group (JTTF + conventional basic treatment) or control group (conventional basic treatment) in a 1:1 ratio. Both groups will have received the same lifestyle interventions in the preceding 12 weeks. The primary outcome will be change in visceral fat area and total score on the TCM syndromes efficacy score scale. The secondary outcome will include changes in ultrasound steatosis grade, fibrosis 4 score (FIB-4), metabolic parameters, anthropometric parameters, visceral fat area. In addition, serum and urine samples collected at baseline and at the end of 12 weeks of treatment will be sequentially tested for untargeted and targeted metabolomics.

**Discussion:** This study will evaluate the efficacy and safety of JTTF, as well as investigate the differential metabolites and possible mechanisms of JTTF treatment in T2DM combined with NAFLD. We hypothesize that patients will benefit from JTTF, which may provide strong evidence for the clinical use of JTTF in the treatment of T2DM and NAFLD, leading to the possibility of further mechanistic exploration.

**Clinical Trial Registration:** This clinical trial has been registered in China Clinical Trial Registry (ChiCTR 2100051174).

## 1 Introduction

The global burden of diabetes continues to rise annually among the general population with a predicted increase from 10.5% (536.6 million people) in 2021 to 12.2% (783.2 million) by the year 2045 in people aged 20–79 years (Sun et al., 2022). According to the epidemiological survey conducted by Li et al. (Li et al., 2020), diabetes is prevalent in 11.2% of the Chinese population. Diabetes and related complications significantly affect quality of life, mortality and morbidity, and contributes to greater economic burden on individuals and society at large (American Diabetes Association, 2018). Non-alcoholic fatty liver disease (NAFLD) is one of the most common chronic liver diseases worldwide and includes various pathological states such as simple steatosis and non-alcoholic steatohepatitis (NASH). The disease is initially accompanied by fat accumulation and may gradually progress to other diseases such as liver fibrosis, cirrhosis, or hepatocellular carcinomas (Chalasani et al., 2018). In the absence of any intervention for NAFLD, human health is endangered and the risk of death increases by at least 71% (Tilg and Targher, 2021). Studies have shown that the prevalence of NAFLD in patients with T2DM is greater than 55% (Younossi et al., 2019), which is 5–9 times higher than the incidence in the general population. Conversely, individuals with NAFLD have a significantly higher risk of developing diabetes than those without NAFLD, which is more than twice as high as that of healthy individuals (Mantovani et al., 2018). More than 60% of patients were found to have abnormal glucose metabolism, leading to a 47.3% probability of diabetes (Buzzetti et al., 2016); thus NAFLD may be an early predictor of T2DM (Lee et al., 2019).

The pathogenesis of T2DM and NAFLD is complex and not yet fully understood. However, it is widely accepted that the two diseases share a common pathogenesis, insulin resistance (IR), both as a cause and a consequence of T2DM combined with NAFLD (Park et al., 2013). Clinical trials developing drugs to treat NAFLD have also focused on the discovery of insulin sensitizers (Ibrahim et al., 2013). Many of the same changes have been shown to occur in the development of both diseases, including abnormal glucose and lipid metabolism, genetic susceptibility, environmental influences, and lifestyle changes (Saponaro et al., 2015). NAFLD is usually treated as a benign disease and neglected for management and treatment. However, when it occurs in combination with diabetes, it exacerbates imbalances in glucolipid metabolism, and abnormalities in glucose and lipid metabolism interact to affect each other. Moreover, diabetes increases the risk of cirrhosis and mortality in patients with NAFLD, while NAFLD increases the incidence of cardiovascular disease and all-cause mortality in patients with T2DM (Radaelli et al., 2018). In the presence of abnormalities in the relevant metabolic and anthropometric indicators, clinical screening for disease should be performed promptly to exclude them. The occurrence of this comorbidity is usually accompanied by abnormalities in glucolipid metabolism-related indicators such as glucose, lipids, and insulin levels (Ziolkowska et al., 2021). Also, some anthropometric indicators are closely associated with the occurrence and development of comorbidity, represented by WHtR (Swainson et al., 2017). Therefore, it makes sense to adopt a holistic approach to the treatment of these metabolic diseases with highly related pathogenesis and pathological manifestations.

Changes in molecular products in the human body can precede the appearance of clinical symptoms (Wu et al., 2019); hence, metabolomics has been gradually applied in recent years to explore disease diagnosis, pathogenesis, and risk assessment (Roberts et al., 2014; Newgard, 2017, 2017; Wishart, 2019; Schmidt et al., 2021). This technique may also identify biomarkers for the early diagnosis of a disease (Esperanza et al., 2020; Cui et al., 2021) or explore metabolic differentials in the action of Chinese and Western drugs (Tao et al., 2019; Wu et al., 2019; Xiao et al., 2020; Xu et al., 2020; Luo et al., 2021; You et al., 2021). Further, it has applications for assessing the variability of molecular metabolic products in patients with different traditional Chinese medicine (TCM) syndromes of the same disease (Guo et al., 2021; Shan et al., 2021). Other studies have applied metabolomic techniques to the diagnosis and mechanistic exploration of diabetes and its complications (Jimenez-Luna et al., 2020; Wang S. et al., 2021; Zhang F. et al., 2021; Tan et al., 2021), and to NAFLD (Masoodi et al., 2021; Piras et al., 2021). Therefore, it is feasible and relevant to study the treatment of this comorbid disease at a molecular level.

The current Western medical treatment of T2DM combined with NAFLD is mainly aimed at reducing fat accumulation in the liver and delaying the onset of inflammation and fibrosis (Ks et al., 2019), and relies on lifestyle management, the application of glucose- and lipid-lowering drugs, and the implementation of bariatric surgery. Glucose management is particularly important for inhibiting the development of liver fibrosis (Nakahara et al., 2014). Lifestyle modification is a basic form of treatment for patients with T2DM and NAFLD. Reducing body mass index (BMI) can effectively improve liver function and insulin resistance levels (Al-Jiffri et al., 2013). However, non-pharmacological therapies often show low compliance in the patient population and are difficult to adhere to. Although there are currently no Food and Drug Administration (FDA)-approved drugs for NAFLD or NAFLD combined with type 2 diabetes (Ferguson and Finck, 2021), many emerging drug therapies such as targeted therapies are in development (Negi et al., 2022). The continuous clinical exploration of drugs for the treatment of NAFLD in combination with T2DM shows the high incidence of this comorbidity and the necessity of treatment. There are many glucose-lowering drugs also used in the treatment of NAFLD in the clinic, such as glucagon-like peptide-1 (GLP-1), Thiazolidinediones, Metformin, which have good effect on fat reduction and glucose reduction (Negi et al., 2022). However, there are still some limitations, for example, metformin has a weak effect on hepatic fat; thiazolidinediones may show weight gain and female fractures despite their insulin-sensitive effects; GLP-1 has a significant weight loss effect but is often accompanied by gastrointestinal side effects. In summary, additional therapeutic strategies are urgently required to treat this complicated disease.

TCM treats diseases from a holistic viewpoint, harmonizing the organs of the whole body in a comprehensive manner. This medicine system has multi-component, multi-target, multi-pathway, prospective, and stable characteristics, and is especially effective in treating complex and variable chronic diseases such as T2DM (Wang X. et al., 2021). Chinese medicine can improve IR and glucolipid metabolic function, among other effects, by regulating the inflammatory response and oxidative stress capacity, and improving the structure of the intestinal flora, thereby treating T2DM combined with NAFLD. It not only improves the clinical index of patients but also alleviates clinical symptoms for the purpose of prevention and treatment. For example, the Chinese botanical drugs such as Shengmaiyin and Ganmai Dazao Tang (Fan et al., 2018; Li et al., 2019), and other appropriate Chinese medicine techniques such as acupuncture and acupuncture point burial are widely used in clinical practice to assist in lowering sugar and reducing fat (Li et al., 2021; Wang et al., 2022).

Jiedu Tongluo Tiaogan Formula (JTTF) is a clinically effective formula based on TCM theory, consisting of the dried rhizome of *Coptis chinensis* Franch [Ranunculaceae; Coptidis rhizome], the dried rhizome of *Rheum palmatum* L [Polygonaceae; Rhei radix et rhizoma], the dried root of *Astragalus mongholicus* Bunge [Fabaceae; Astmgali radix], the dried rhizome of *Salvia miltiorrhiza* Bunge [Lamiaceae; Salviae miltiorrhizae radix et rhizoma], the dried root of *Bupleurum chinense* DC [Apiaceae; Radix bupleuri], at the weight ratio of 15:9:15:15:10. This formula is involved in detoxifying and regulating the draining function of the liver to eliminate the “toxic evil” in the body for disease prophylaxis and treatment. The effectiveness of this formula in lowering blood glucose, regulating blood lipids, promoting insulin secretion, and improving IR has been verified in many basic and clinical trials.

The main components of JTTF have been analyzed by High Performance Liquid Chromatography (HPLC) in our previous study (Zhang Q. et al., 2021), which can be seen in Supplementary Material S1. On the basis of reference standard data, chromatographic elution behavior, chemical composition data, mass fragmentation pattern and HPLC results, the chemical components of JTTF were identified as chlorogenic acid, anthocyanin-7-glucoside, tannic acid B, aloe rhodopsin and haragoside. By means of the validation of network pharmacology and in vitro experiments, it proves that JTTF plays an important role in promoting insulin secretion and regulating glucolipid metabolism by acting on the PI3K-Akt pathway, an important pathway for insulin signaling and glucose regulation (Zhang Q. et al., 2021). Related research has demonstrated that JTTF can inhibit the expression of inflammatory factors associated with endoplasmic reticulum stress, thereby alleviating this condition (Jiang et al., 2018), improving IR, and increasing insulin sensitivity (Liu et al., 2021). At the same time, it can activate the IRE1α/JNK pathway, which is closely related to IR and pancreatic β-cell apoptosis to reduce the apoptosis of pancreatic islet cells and prevent and treat T2DM (Piao et al., 2018). Studies showed that blood glucose and lipid levels, as well as IR levels of diabetic ZDF rats were significantly improved by high-dose JTTF (Liu et al., 2021). Related clinical studies have shown that JTTF may reduce glycated hemoglobin, blood glucose, and inflammatory factor levels, regulate lipid and insulin resistance levels in T2DM patients (Jin et al., 2020), and have significant efficacy in reducing liver function, BMI, waist circumference, and TCM symptom scores in T2DM combined with NAFLD patients (Gong, 2017).

Herein we investigate the clinical efficacy and safety of JTTF for the treatment of T2DM combined with NAFLD. It is necessary to design and conduct this trial study as the mechanism of action of this formula has not been explored at the molecular level.

## 2 Methods and analysis

### 2.1 Study objectives

#### 2.1.1 Primary objective

The primary objective of this clinical trial is to assess the efficacy and safety of JTTF for the treatment of T2DM combined with NAFLD. We hypothesized that JTTF combined with conventional Western medicine would be more effective than the single use of conventional Western medicine alone in reducing fat accumulation, inhibiting liver fibrosis, regulating blood lipids, lowering blood glucose levels, and alleviating the clinical symptoms of patients with T2DM and NAFLD.

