#### 2.8.3 Secondary outcomes

1) Changes in hepatic steatosis factors by ultrasound grading of steatosis.2) Changes in metabolic parameters: glycated hemoglobin (HbA1c) levels, fasting plasma glucose (FPG), 2-h plasma glucose (2h-PG), fasting insulin, blood lipids including total cholesterol (TC), triglycerides (TG), high-density lipoprotein-cholesterol (c-HDL), low-density lipoprotein (c-LDL), apolipoprotein A (ApoA), and apolipoprotein B (ApoB).3) Changes in anthropometric parameters: Waist-to-height ratio (WHtR), Body Mass Index (BMI), waist circumference (WC), hip circumference (HC).4) Changes in hepatic fibrosis factors and hepatic function: The changes in Fibrosis 4 Score (FIB-4, http://gihep.com/calculators/hepatology/fibrosis-4-score/) can be calculated by the formula:

$$\mathrm{Age}\;\left(\mathrm{years}\right)\text{x}\;\mathrm{AST}\;/\mathrm{PLT}\;\left(\times 10^{9}/L\right)\text{x}\sqrt{\mathrm{ALT}}$$

The units of measurement for ALT and AST are aligned with those for age and PLT.

Definitions for the following abbreviations: AST: Aspartate aminotransferase; PLT: platelet; ALT: Alanine aminotransferase.5) Changes in visceral fat area.

All measurements will be performed at baseline and at week 12. Additional FPG and blood lipid test will be performed at week 6.

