### 2.10 Sample size calculation

In a previous study (Xu, 2017), JTTF reduced HbA1c levels in diabetic patients with heat stagnation in liver and stomach after 12 weeks of treatment (treatment group: 6.94±0.88%, control group: 7.64±0.72%, mean difference between the two groups: 0.7%). Considering a type I error of 5% (α = 0.05) and a power of 85%, the experimental and control groups were allocated at a ratio of 1:1. The sample size was calculated using Power Analysis and Sample Size (PASS) software (version 15.0); a total of 76 patients will be required. According to the dropout rate of 20%, we set the final sample size to 96, with 48 patients in each group, considering the number of dropout samples.

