## 3 Statistical methods

### 3.1 Data analysis

Data will be analyzed using SPSS software (Version 24.0; IBM Corp. Armonk, NY, United States). Continuous variables will be represented as means, standard deviations, medians, and minimum/maximum values. If the data confirms normal distribution, an independent sample *t*-test will be used to assess the differences between the two groups, and a paired sample *t*-test to compare the differences between groups before and after the intervention. Wilcoxon signed-rank test will be used for data that does not conform to normal distribution. Grade data will be analyzed using Wilcoxon’s signed-rank test or the CMHχ2 test. Statistical significance will be set at *p* < 0.05.

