## 4 Discussion

NAFLD has a high prevalence worldwide, affecting approximately 25% of the population (Younossi et al., 2021). It is extremely harmful, especially when combined with diabetes, and significantly increases the risk of developing cirrhosis and liver cancer as well as the mortality rate (Golabi et al., 2018; Younossi and Henry, 2019). However, there are still no safe and effective drugs for the treatment of T2DM in combination with NAFLD (Ferguson and Finck, 2021). The current first-line interventions for both NAFLD, and T2DM with NAFLD remains lifestyle modification and weight loss, which also has the disadvantages of low compliance and difficulty in long-term implementation. Therefore, there is a need for a protocol that systematically treats T2DM combined with NAFLD as a comorbid disease, while improving clinical symptoms and combining metabolomics to identify targeted pathways of action to regulate glucose and lipid metabolic abnormalities.

This study is a double-armed, parallel-designed, randomized, controlled clinical trial that aimed to verify the efficacy and safety of JTTF for glucose-lowering and lipid-modulation and to investigate the differences in serum and urine metabolites before and after treatment. The proposed protocol combines clinical evaluation with metabolomics in an attempt to determine its mechanism of action and pathway of action, offering the possibility to systematically elucidate the effectiveness and mechanisms of action of JTTF. Considering the limitations of liver biopsy implementation, this study focused on subjects with fatty liver diagnosed by ultrasound to observe changes in visceral fat and subcutaneous fat area. In addition, patients’ blood lipids, liver function, BMI, HbA1c level, blood glucose, TCM symptom scores, and other indicators will be assessed, and the degree of fibrosis and insulin resistance will be evaluated. Disease onset and progression will be comprehensively evaluated in this clinical study.

This study has some limitations. First, coronavirus outbreaks remain a serious concern worldwide and may affect patient follow-up. In addition, this is a single-center study conducted in China; therefore, the generalizability of the findings remains unclear. Finally, the clinical application of JTTF should be expanded to provide evidence for further mechanistic studies.

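### The primary hypothesis claims lipid, glucose and fibrosis effects that no primary outcome measures; these rest on secondary outcomes judged at a flat p < 0.05

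*Protocol article*

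**What the plan says.** Section 2.1.1, under the heading of the primary objective, states one hypothesis with five parts: JTTF plus conventional treatment is expected to do better than conventional treatment alone "in reducing fat accumulation, inhibiting liver fibrosis, regulating blood lipids, lowering blood glucose levels, and alleviating the clinical symptoms".

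Section 2.8.2 names two primary outcomes, the change in visceral fat area (VFA) and the TCM syndromes score. Section 2.8.3 lists the following as secondary:
- three glucose measures: HbA1c, fasting plasma glucose (FPG) and 2-hour glucose;
- fasting insulin;
- six lipids: TC, TG, HDL-C, LDL-C, ApoA and ApoB;
- FIB-4, for fibrosis.

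These are measured at baseline and week 12, and the section adds: "Additional FPG and blood lipid test will be performed at week 6".

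Section 2.10 sizes the trial on HbA1c ("treatment group: 6.94±0.88%, control group: 7.64±0.72", in per cent), which is a secondary outcome. Section 3.1 gives one decision threshold without separating primary from secondary outcomes: "Statistical significance will be set at *p* < 0.05". The Discussion describes the study as a trial that "aimed to verify the efficacy and safety of JTTF for glucose-lowering and lipid-modulation".

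**The concern.** Two of the five parts of the hypothesis have a primary outcome: VFA for fat accumulation and the TCM score for symptoms. The other three (fibrosis, lipids, glucose) have none. Sections 2.1.1 and 2.10 and the Discussion treat glucose as a main efficacy question, and 2.1.1 and the Discussion do the same for lipids. Sections 2.8.2 and 2.8.3 rank both below VFA and the TCM score.

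The article does not say what result would count as regulating lipids or lowering glucose. If VFA and the TCM score showed no effect but one of several lipid or glucose tests fell below 0.05, the current wording would let that result be presented as support for the primary hypothesis. What is at stake is which conclusions the trial may draw, and at what error rate.

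**Working it through.** **Step 1. Match the hypothesis to the outcomes.**

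| Part of the hypothesis (2.1.1) | Primary outcome (2.8.2) | Secondary outcomes (2.8.3) |
|---|---|---|
| Fat accumulation | VFA | ultrasound steatosis grade |
| Liver fibrosis | none | FIB-4 |
| Blood lipids | none | 6 lipids |
| Blood glucose | none | 3 glucose measures |
| Symptoms | TCM score | – |

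**Step 2. Inputs for the error rate.**
- Per-test level: 0.05 (3.1; the same α appears in 2.10). The sides are not stated; two-sided is assumed, so the critical value is 1.96.
- Number of tests k at week 12: 3 glucose, 6 lipid, 9 together. Fasting insulin is left out because it is not a glucose level. Week 6 is left out because the article states a measurement then, not an efficacy test.
- Correlation ρ between test statistics: not in the article. A common ρ of 0, 0.5 and 0.8 is assumed.
- Claim rule: one significant marker is enough. This is also an assumption.
- The sample-size total in 2.10 does not enter this calculation.

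**Step 3. Formula.** With no true effect and independent tests, the chance of at least one p < 0.05 is 1 − 0.95^k. For k = 1 this returns the plan's own 0.05. For favourable results only, it is 1 − 0.975^k.
- k = 3: 1 − 0.95³ = 0.143; favourable 1 − 0.975³ = 0.073
- k = 6: 1 − 0.95⁶ = 0.265; favourable 1 − 0.975⁶ = 0.141
- k = 9: 1 − 0.95⁹ = 0.370; favourable 1 − 0.975⁹ = 0.204

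For ρ > 0, write each statistic as √ρ·U + √(1−ρ)·Eᵢ with independent standard normal U and Eᵢ. Given U, the tests are independent, so the chance that none is significant is the conditional non-rejection probability to the power k, averaged over U.

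**Step 4. Results** (either direction, with favourable only in brackets).

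| Tests | ρ = 0 | ρ = 0.5 | ρ = 0.8 |
|---|---|---|---|
| 3 glucose | 14.3% (7.3%) | 12.5% (6.3%) | 9.8% (4.9%) |
| 6 lipids | 26.5% (14.1%) | 20.7% (10.4%) | 13.9% (6.9%) |
| 9 together | 37.0% (20.4%) | 26.9% (13.5%) | 16.6% (8.3%) |

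As multiples of 5%, the either-direction range is 16.6/5 = 3.3 to 37.0/5 = 7.4 for the nine tests, 2.0 to 2.9 for glucose and 2.8 to 5.3 for lipids.

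**Step 5. Sensitivity to the correlation pattern.** If measures correlate only within a domain and glucose is independent of lipids, the nine-test figure is about 31% at ρ = 0.5 and 22% at ρ = 0.8. Both lie inside the range above.

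**The case against.** The strongest reply is that only a journal article is at hand. The order of testing, the handling of α and an exploratory label for secondary outcomes are commonly left to an analysis plan, which is not shown. The glucose and lipid outcomes already carry the label secondary, and unadjusted testing of labelled secondary outcomes is widespread. This stands: the absence of a hierarchy is not, by itself, a finding. It does not remove the conflict between 2.1.1, 2.8.2 and the Discussion, which is in the current text. An analysis plan does not normally rewrite the primary hypothesis.

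A reader might also infer more than the article supports:
- **That a false lipid or glucose claim is about five times as likely as 5%.** No single multiple fits. It depends on which tests are counted, the direction and a correlation that the article does not give. Glucose alone never reaches five times.
- **That one significant marker would be claimed as efficacy, even after null primary results.** The article states no such rule. It leaves the reading open.
- **That the week-6 measurements add seven tests.** Sixteen tests would give roughly 21% to 56%, but no efficacy test at week 6 is stated.
- **That the Discussion claims efficacy.** It states an aim, not a result.

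Lowering glucose is also a directional claim. Counting only favourable results halves the rates, and for glucose they are then 4.9% to 7.3%. The comparable rate for one two-sided test is 2.5% in that direction, so some inflation remains, but in absolute terms it is small for glucose.

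**Conclusion.** The point holds as a mismatch between the primary hypothesis and the primary outcomes. Three of the five hypothesised benefits have no primary outcome, and the only decision rule given for them is p < 0.05 on each test. The error rates in the working show what that would cost if one nominally significant week-12 marker were accepted as support. For results in either direction the rate exceeds 5% in every scenario tried. The ranges depend on two-sided tests and on the assumed correlation and claim rule, none of which the article states. The comparisons on VFA and the TCM score are not affected. What needs correcting is what the trial may conclude about lipids, glucose and fibrosis.

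**What to change.** 1. Reword 2.1.1 and the matching sentence in the Discussion so that the confirmatory hypothesis covers only VFA and the TCM score.
2. State in 2.8.3 and 3.1 that glucose, lipid and fibrosis results are secondary and supportive, are reported as estimates with 95% confidence intervals, and cannot establish efficacy if the primary analysis fails.
3. Optional: if a confirmatory glucose or lipid claim is wanted, name one measure of each at week 12 (for example HbA1c, already used in 2.10) and test them in a fixed order, only after primary success. This is one workable choice, not a required correction.

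The cost is a few sentences, with no extra patients or data. The downside is that a nominally significant lipid, glucose or fibrosis result outside the named set can no longer be presented as confirmed.
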